### Interventions

#### Neuromuscular training program (NEMEX-TJR training program)

The neuromuscular training follows the principles of neuromuscular and biomechanical training as described in the neuromuscular training method NEuroMuscular EXercise (NEMEX) [24], and aims to improve neuromuscular control (also called sensorimotor control) and to achieve compensatory functional stability. Neuromuscular control is defined as the ability to produce controlled movement through coordinated muscle activity. Movement starts with the non-affected leg to facilitate the bilateral transfer effect of motor learning. Exercises are mainly performed in closed kinetic chains in the lying, sitting or standing position to achieve muscular co-activation in an appropriate position of the joints with hip, knee and foot well aligned. These activities emphasize the improvement of the stabilizing functions of the weight-bearing muscles for better postural control in static and dynamic situations. Open kinetic chains are only performed to improve muscle strength of the knee and hip muscles.

The training takes place in groups under the supervision of an experienced and especially trained physical therapist and consists of three parts:

• Part 1 Warming up: The warm-up period consists of ergometer cycling for 10 minutes. The workload is set individually and can be increased during the 10 minutes.

• Part 2 Circuit program: The circuit program comprises four exercise circles, with the key elements: core stability/postural function, functional alignment, lower-extremity muscle strength and functional exercises. Usually two exercises, sometimes one, are performed in each circle. Each exercise is performed 2–3 sets * 10–15 repetitions, with rest between each exercise and circle. To allow progression three levels of difficulty are defined. Progression is provided by varying in number, direction and velocity of the movements, by increasing the load and/or by changing the support surface. Progression is made when an exercise is performed of 3 sets * 15 repetitions with good neuromuscular control and good quality of performance (based on visual inspection by the physical therapist) and with minimal exertion and control of the movement (perceived by the patient).

• Part 3: Cooling down: The cooling down period of about 10 minutes consists of forward and backward walking exercises, about 10 meters in each direction, mobility exercises for the lower extremities and stretching exercises for the lower-extremity muscles.

The exercises included in the training program are described in detail in the Additional file 1[24].

Documentation of the training program includes the number of training sessions, level of difficulty per session, pain on a 0 to 10 scale before and after each session and 24 hours after each session.

Patients also document how physically active they were per training week (activity levels A-C), notified in minutes per activity level. Level A consists of competitive sports activities, intensive enough to cause heavy sweating. Level B consists of endurance or muscle strengthening activities, intense enough to cause light sweating and faster breathing while still allowing one to talk, i.e. increased walking, running, cycling, swimming, cross-country skiing or muscle strength training. Level C consists of activities of daily living, i.e. walking, climbing stairs, housekeeping or garden work [25].

#### Knee school

The knee school was designed to educate participants about knee OA, the preparation phase before undergoing TKR and the acute rehabilitation phase afterwards. The concept of the knee school is adapted from the hip school, described by Klassbo [26]. The knee school is taught by an experienced and especially trained physical therapist over 3 individual or group sessions, one session per week, starting about 4 weeks before the operation. Knee school sessions are separately organised for participants of the intervention group and those of the control group to avoid contamination.

The content of the school includes information about anatomy of the knee joint and adjacent functional structures, recommended activities with prosthesis and postoperative pain management, and details on the postoperative rehabilitation phase. Didactical elements include models of the knee joint and the lower extremity, working sheets, photos and videos, hand outs, PowerPoint presentations and peer discussions.

#### Intervention group

Participants of the intervention group receive 8–24 sessions of the neuromuscular training program prior to TKR surgery depending on location of the waiting list for surgery. Participants also receive 3 sessions of the knee school starting about 4 weeks before surgery.

### Control group

Participants of the control group receive 3 sessions of the knee school, starting about 4 weeks before surgery.

#### Outcome measures

We include one objective (Chair Stand Test) and two patient-reported outcome measures (pain and function subscale of the KOOS questionnaire) in this trial to test the effect of the intervention on lower extremity function (see Table 1).

**Table 1 T1:** Summary of measures to be collected

**Primary outcome measure**	**6**–**12 weeks pre**-**op**.	**1 week pre**-**op**.	**at discharge**	**6 weeks post**-**op**.	**3 months post**-**op**.	**1 year post**-**op**.
Chair Stand Test	X	X			X	
**Secondary outcome measure**						
Subscales pain and function of the KOOS	X	X		X	X	X
**Additional outcome measures**						
Muscle strength	X	X			X	
Knee-bending/30s	X	X			X	
Range of motion of the knee	X	X			X	
20m walk test	X	X			X	
Timed up and go	X	X			X	
Physical activity level	X	X		X	X	X
Adapted NHANES III	X	X		X	X	X
SF 36	X	X		X	X	X
EQ-5D	X	X		X	X	X
RAPT	X					
LOS			X			
Minutes of nursing care			X			

KOOS Knee injury and Osteoarthritis Outcome Score.

NHANES National Health And Nutrition Examination Survey.

SF 36 Short Form-36 health survey.

EQ-5D EuroQol – 5 dimensions.

RAPT Risk Assessment and Predictor Tool.

LOS Length of stay.

#### Primary outcome measure

The primary outcome is the Chair Stand Test, also known as the repeated sit-to-stand test. It is commonly used as a measure of lower extremity strength, balance and reaction time [27-29]. The subject is asked, to stand up from a chair without armrests to a fully erect standing position five times as quickly as possible without pushing off [30]. The time needed is measured by a stop watch in seconds. The Chair Stand Test is easy to perform in clinical practice and has shown excellent intra- and inter-rater reliability (Inter Class Correlation, 0.89 [31]. The Chair Stand Test was also found to predict disability across populations accurately [32].

#### Secondary outcome measure

Secondary outcomes are knee pain and function assessed by the KOOS questionnaire. The KOOS is a commonly used patient-reported outcome with overall acceptable psychometric properties to evaluate patients with knee injury and knee OA [33], including those having TKR [34]. KOOS holds 5 subscales with a total of 42 items: 1) pain, 2) other symptoms, 3) function in daily living (ADL), 4) function in sport and recreation and 5) knee-related quality of life. Since exercise training is aiming to improve function we are particularly interested in the KOOS ADL subscale for the functional outcome measure.

The German version of the KOOS is used in this trial [35]. Its user’s guide including scoring instructions, are available from http://www.koos.nu.

#### Additional outcome measures

##### Lower limb function

Isometric muscle strength of knee flexors and extensors, hip flexors, hip extensors, hip adductors and hip abductors are measured with a hand-held pull gauge [36,37]. The ability to alternate rapidly between concentric and eccentric work of the extensor muscles of the hip and knee is impaired in many patients with knee OA [38]. The ability of rapid alternation between concentric and eccentric function is measured using maximal number of knee-bending in 30 seconds, which is a valid and reliable test (ICC, 0.80) [24,39]. Range of motion is measured with a long-arm goniometer [40]. Walking speed is assessed with the 20m walk test (ICC, 0.93) [24], a reliable modification of the short walk test used in many epidemiological and clinical studies. The test measures the time it takes to walk 20 meters at the participant’s usual walking pace, along with the number of steps that they take to walk 20 meters [41]. Lower extremity mobility is further assessed with the Timed Up and Go test, which requires a person to rise from a stair, walk 4 meters, turn 180°, return to the chair and sit down [42].

##### Physical activity and health-related quality of life

Physical activity is measured by the SenseWear armband, a device for quantifying physical activity in daily life [43,44]. It collects the following data: energy expenditure, average MET’s, physical activity duration, steps per day and the physical activity distribution (sedentary, moderate, vigorous and very vigorous). In addition, physical activity is measured by 10 activity questions assessed and validated in NHANES III [45,46]. Health-related quality of life is measured by the generic questionnaire SF-36 [47,48]. General health status is measured by the EuroQoL (EQ-5D). The EQ-5D is used to complement the SF-36, allowing health economic evaluation and comparison to other knee OA populations [49].

##### Health service utilization

Discharge potential is measured by the Risk Assessment and Predictor Tool (RAPT), a 6 question tool which scores patients into low, middle or high risk for extended inpatient rehabilitation [23].

Length of Stay (LOS) and minutes of care by the nursing staff (including all activities delivered to the patients, e.g. mobilisation, washing, medication) are measured by LEP^®^, which is a tool used for workload management in nursing [50]. Both measurements are taken at discharge in the acute care hospital.

### Sample size calculation

The sample size calculation is based on the primary endpoint - the Chair Stand Test. We assume that the mean difference in change over time between groups is 7.3 seconds (corresponding to means of 8.3 and 1.0, respectively) and the common within-group standard deviation is 7.3. This effect was selected based on pilot data of an uncontrolled trial in knee OA patients [24], assuming that our control group (without exercise training) would not improve over time while awaiting TKR. It is also assumed that the effect size is reasonable, in the sense that an effect of this magnitude could be anticipated in this field of research. Alpha has been set at 0.05 and the power has been set at 0.9. In each group 25 patients are needed.

Assuming a drop-out rate of 12%, we will include 40 patients per group.

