## Background

Osteoarthritis (OA) is the most common joint disorder and a common cause of pain, loss of function and disability in older adults [1]. It is the second most common diagnosis made in older adults seeking medical care [2] and the leading cause of disability at older age [3]. When suffering from severe OA, Total Joint Replacement (TJR) is the preferred treatment option to significantly improve function and pain [2,4]. Given the demographic change with growing segment of the senior population in the Western World, the rate of these procedures will rise exponentially over the next decade. This will result in high health-care expenditures due to the absolute increase in TJR surgery (both direct hospital charges and indirect costs) [5].

The current EULAR (European League Against Rheumatism) recommendations include exercise as an effective treatment in the improvement of pain and function in patients with moderate to severe knee OA (effect size for validated outcome measures of pain and function versus placebo range from 0.57 to 1.0) [6]. Similarly, the OARSI (Osteoarthritis Research Society International) supports the benefits of exercise in patients with knee OA, both on pain and function [7].

Notably, exercise alone may delay but not prevent TJR in severe OA [8]. Similarly, however, TJR does not fully restore function in many patients undergoing the procedure [9-11], which in part may be due to long-term mechanical impairments of the joint.

The most recent review published on pre-operative interventions for patients with hip or knee osteoarthritis awaiting joint replacement was published in 2011 and included 23 trials [12]. The authors concluded that there was low to moderate quality evidence for the benefit of pre-operative exercise for Total Knee Replacement (TKR). These data are consistent with three earlier systematic reviews [13-15].

Considering the evidence from the available formal reviews, two factors may have prevented a benefit from these programs: (A): Four trials had very small groups with a combined total of 137 subjects and were probably underpowered [16-19]. (B): The therapeutic validity as described by Hoogeboom et al. was not sufficient enough, making it unlikely, that interventions evaluated in these studies would have relevant effects [20].

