### Analysis plan

All analyses are based on intent-to-treat, including all randomized individuals who had at least 1 intervention session. We will use linear regression to evaluate the effect of our training program plus knee school against knee school alone for both the primary and secondary endpoints – after the training and at 3 months after surgery. The multivariate analyses for the primary endpoint (Chair Stand Test) and secondary endpoints (pain and function subscales of the KOOS) will control for baseline function of the respective endpoint, age in years, gender, and baseline body mass index. To account for the reduced exposure time to the training intervention for participants who were on a short waiting list or were less adherent we will perform subgroup analyses by training exposure groups (we will use the median as a cut-off for lower and higher intensity of the training program based on number of training sessions attended).

To evaluate a benefit of the training program on patient-reported pain and function across all time points, we will use repeated measures linear regression analyses controlling for baseline strength/function, time, age, gender, and body mass index.

Analyses will be conducted with R version 2.14.1 software. All P values are two-sided.

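### A 12% drop-out allowance takes 25 per group to 29, not to the 40 that the sample size paragraph derives from it

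*Protocol article*

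**What the plan says.** The section Sample size calculation bases the trial's size on the Chair Stand Test alone. It assumes that "the mean difference in change over time between groups is 7.3 seconds (corresponding to means of 8.3 and 1.0, respectively"), and that "the common within-group standard deviation is 7.3". It continues: "Alpha has been set at 0.05 and the power has been set at 0.9. In each group 25 patients are needed". The closing sentence of the section moves from that number to the enrolment target: "Assuming a drop-out rate of 12%, we will include 40 patients per group". The abstract gives the same target as a total of 80. Sidedness is not stated in the sample size section, but the Analysis plan says "All P values are two-sided".

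Neither the sample size section nor any other part of the article names a secondary endpoint, a subgroup, a later time point or any other consideration as a reason for enrolling more patients than the drop-out allowance requires.

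**The concern.** The last sentence presents 12% drop-out as what takes 25 to 40. A 12% allowance adds three or four patients per group to 25, not fifteen. All the inputs are printed, so this is not a detail that a condensed article leaves to the full protocol; the printed figures do not lead to the printed result.

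At stake is the stated justification for the trial's size. A reader cannot tell whether 40 reflects a much larger expected loss, a deliberate enlargement for a reason not given, or a slip. These differ in how much attrition the trial is meant to tolerate and in how many evaluable patients it expects. An ethics committee or a patient also cannot see from the text why 80 people are asked to take part when the stated inputs call for 58.

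**Working it through.** **Inputs.** From Sample size calculation: difference 7.3 s (8.3 − 1.0), SD 7.3 s, alpha 0.05, power 0.90, 25 needed per group, drop-out 12%, 40 enrolled per group. From Analysis plan: two-sided tests. Equal allocation follows from the equal group sizes.

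**Step 1: the plan's base figure.** Standardised difference d = 7.3/7.3 = 1.0.

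- Normal approximation: n = 2(z₀.₉₇₅ + z₀.₉₀)²/d² = 2(1.960 + 1.282)² = 21.02, rounded up to 22 per group.
- Two-sample t-test (noncentral t): n = 22.02, rounded up to 23 per group. Power is 0.8997 at 22, 0.912 at 23 and 0.934 at 25.

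The stated 25 meets the 90% requirement with a small margin. It is close to the t-test result and errs on the safe side.

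**Step 2: the drop-out allowance.**

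- Standard inflation: 25/(1 − 0.12) = 28.4, rounded up to 29 per group, 58 in total.
- The cruder form: 25 × 1.12 = 28 per group.
- Stated: 40 per group, 80 in total. The excess over 58 is 80 − 58 = 22 patients, or 22/80 = 27.5% of enrolment.
- Loss rate that would turn 25 into 40: 1 − 25/40 = 0.375, about three times the stated rate.

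**Step 3: can another reading give 40?**

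| Reading | Per group |
|---|---|
| 25 already includes drop-out (22/0.88 = 25) | 25; the step to 40 is then still less explained |
| 12% lost at each of the two follow-up Chair Stand Tests in Table 1 | 25 × 1.12² = 31.4, so 32; or 25/0.88² = 32.3, so 33 |
| Alpha halved to 0.025 for two time points | 25 (normal) or 27 (t); 29 or 31 after 12% loss |
| One-sided test | base n of 18, further from 40 |

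Four successive multiplications by 1.12 give 39.3, but the text states a single rate and the Chair Stand Test has only two follow-up assessments. None of these readings is stated, and none gives 40 on the document's own terms.

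**Step 4: what 40 per group delivers.**

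- With 12% loss: 40 × 0.88 = 35.2, so about 35 evaluable per group. Power at 7.3 s (t-test) is 0.985. The difference detectable with 90% power is 0.786 × 7.3 = 5.7 s.
- With 37.5% loss: 40 × 0.625 = 25 evaluable per group. Power at 7.3 s is 0.934.

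**The case against.** The strongest reply is that the discrepancy is harmless. Enrolling 40 when 29 would do leaves about 35 evaluable per group, more than the 25 needed, so the trial meets its power requirement for 7.3 s with room to spare. No analysis changes. This stands, and it limits the consequence. It does not make the sentence right, because the text offers 12% drop-out as the derivation of 40 and it is not one.

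Several stronger readings are tempting, and the documents do not support them.

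- **That 25 is also wrong, because the inputs need 22 or 23.** A slightly conservative number that gives 93% power satisfies the stated 90% and needs no correction.
- **That enrolment, power, drop-out and target difference contradict one another.** They can all hold if 90% is read as a minimum. What is missing is the reason for the surplus over 29.
- **That the 1.0 s control change is an error.** The section justifies its effect by "assuming that our control group (without exercise training) would not improve over time while awaiting TKR" yet enters 1.0 s for controls. This is loose wording on the conservative side: a value of zero would make the difference 8.3 s and lower the required number. It has no bearing on 25 against 40.
- **That the trial is weak against the effects the Background cites.** The "effect size for validated outcome measures of pain and function versus placebo range from 0.57 to 1.0" concerns exercise against placebo on pain and function measures, not change in the Chair Stand Test against knee school in patients awaiting surgery. Whether d = 1.0 is optimistic is a separate question.

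**Conclusion.** The concern holds for the step from 25 to 40. As written, 12% drop-out supports 29 per group (58 in total), and 22 of the 80 patients have no stated basis. Reaching 40 from 25 needs 37.5% loss or a reason that the article does not give.

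A reader might infer that the trial is underpowered; under its own assumptions it is not. With 12% loss, power at 7.3 s is about 98%; with 37.5% loss it is about 93%. A reader might also take 5.7 s as the effect the trial was really designed to detect. That value is only back-calculated from 35 evaluable per group. The document treats 7.3 s, taken from pilot data, as the target.

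The drop-out arithmetic needs no assumption beyond the printed figures. The power figures assume an unadjusted two-sample t-test, two-sided alpha 0.05, SD 7.3 s and equal loss in both groups. They ignore the planned adjustment for baseline function, age, gender and body mass index. The documents do not show whether the drop-out rate or the explanation is what went wrong.

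**What to change.** Keep 80 patients, 25 as the base number and 7.3 s as the target, and restate the last sentence of Sample size calculation so that the figures agree. The sponsor must say which of these applies:

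1. **12% is the intended rate.** State that 25 per group inflated for 12% drop-out is 29, that 40 per group are enrolled for a reason which is then named, and that about 35 evaluable per group give about 98% power at 7.3 s (SD 7.3, two-sided alpha 0.05).
2. **A larger loss was intended.** Correct the drop-out rate to the one that yields 40, which is 37.5%.

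The 5.7 s figure may be reported as a consequence of the first option but should not replace the target difference. The cost is wording only: enrolment, outcomes and analyses are unchanged, and the abstract's total of 80 stays as it is.

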### Analysis plan

All analyses are based on intent-to-treat, including all randomized individuals who had at least 1 intervention session. We will use linear regression to evaluate the effect of our training program plus knee school against knee school alone for both the primary and secondary endpoints – after the training and at 3 months after surgery. The multivariate analyses for the primary endpoint (Chair Stand Test) and secondary endpoints (pain and function subscales of the KOOS) will control for baseline function of the respective endpoint, age in years, gender, and baseline body mass index. To account for the reduced exposure time to the training intervention for participants who were on a short waiting list or were less adherent we will perform subgroup analyses by training exposure groups (we will use the median as a cut-off for lower and higher intensity of the training program based on number of training sessions attended).

To evaluate a benefit of the training program on patient-reported pain and function across all time points, we will use repeated measures linear regression analyses controlling for baseline strength/function, time, age, gender, and body mass index.

Analyses will be conducted with R version 2.14.1 software. All P values are two-sided.

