**Figure 1 F1:**
[figure not shown]
Flow chart of research design.

Outcomes are measured at baseline (6–12 weeks pre-operative: primary and secondary endpoints), 1 week pre-operative (after the intervention: primary and secondary endpoints), 6 weeks after surgery (secondary endpoints only), 3 months after surgery (primary and secondary endpoints) and 1 year after surgery (secondary endpoints only).

Prior to the baseline assessment eligible patients receive an information package on the study. The package includes detailed information, including their rights when participating in a research project and a written informed consent form. Ethic approval was granted by the Ethics Committee of the Cantons Aargau and Solothurn, Switzerland, approval number 2009/012.

Reporting of the RCT follows the recommendations of CONSORT guidelines for reporting of clinical trials and will be based on intent-to-treat [21]. In addition, a per-protocol analysis will be performed.

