## Discussion

This randomized controlled trial will compare the effect of pre-operative neuromuscular training plus knee school with knee school alone on lower extremity function. The feasible training program aims to improve the activity-oriented outcome measures. The knee school serves both as an addition to the training as well as an attention control strategy in the control group. As an integral part of this trial, we assess adherence to the training intervention, which will allow per protocol analyses in addition to the primary intent-to-treat analyses.

OA is a key driver of disability at older age and is the fourth most common condition in older women and the eight most common in older men [6,51]. Given the demographic development with a rising segment of the senior population, and therefore improving functionality in individuals with OA is a public health target. Our trial aims to contribute important knowledge on whether to what extend a pre-operative training among patients on a waiting list for TKR will improve their functionality before and after surgery. The interest in the effect of pre-operative interventions has increased in the last decade, which is seen by the increasing number of publications. The evidence is up to now for different reasons moderate and a conclusive answer is not yet possible [12,52].

Our trial will also contribute to evidence-based guidelines to help physicians and patients make informed decisions [53]. With respect to patient functional status, the major predictor of patient functional status postoperatively is pre-operative status [54]. It is therefore important to test the benefit of pre-operative training in patients undergoing TKR and our trial could contribute to a definition of pre-operative treatment recommendations or guidelines.

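### The set labelled intent-to-treat drops randomised patients who attended no session, so it is a modified intent-to-treat set, and exclusion from it can differ between the arms

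*Protocol article*

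**What the plan says.** The Analysis plan section fixes the analysis set for every analysis in one sentence: "All analyses are based on intent-to-treat, including all randomized individuals who had at least 1 intervention session".

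Two other sections state the principle without that condition. The Design section (text below Figure 1) says "Reporting of the RCT follows the recommendations of CONSORT guidelines for reporting of clinical trials and will be based on intent-to-treat" and adds a separate adherence-based analysis: "In addition, a per-protocol analysis will be performed". The Discussion treats the intent-to-treat analysis as the main one, since adherence is recorded in a way "which will allow per protocol analyses in addition to the primary intent-to-treat analyses".

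The sessions offered differ by arm. Under Intervention group: "Participants of the intervention group receive 8–24 sessions of the neuromuscular training program prior to TKR surgery", plus 3 knee school sessions from about 4 weeks before surgery. Under Control group: "Participants of the control group receive 3 sessions of the knee school, starting about 4 weeks before surgery". Baseline is 6–12 weeks before surgery (Design). Under Baseline assessment and randomization, the coordinating investigator tells each participant the allocation and then schedules the sessions.

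**The concern.** Whether a patient attends a first session is settled after randomisation. Selecting on it can undo the balance that randomisation provides, and a set selected in this way is not intent-to-treat. Such a filter is usually defended on the ground that exclusion cannot depend on the arm, for example because nobody knows the allocation before first treatment. That defence is not available here. Participants know their arm before any session; the blinding described is that of the assessors.

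The rule is also not fixed well enough to apply. The article does not say what an intervention session is. If it meant training only, no control patient could qualify, so it must count different things in the two arms.

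At stake is the primary Chair Stand comparison, together with all others, because the sentence covers every analysis. The result would be reported as intent-to-treat when it is not.

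**Working it through.** **The plan's own figure.** The Sample size calculation section assumes a difference of 7.3 s, SD 7.3 s, alpha 0.05 and power 0.90, and arrives at 25 per group. A two-sided two-sample t-test needs 23 per group (power 0.912), and 25 gives 0.934, so the stated figure is close and slightly conservative. The step to 40 per group does not follow from 12% drop-out (25 / 0.88 = 28.4, so 29), but nothing below depends on it.

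**Power is not the issue.** At the protocol's own effect, power is 0.993 with 40 per arm and 0.985 with 35 (40 × 0.88 = 35.2). With 2, 4 or 6 patients per arm excluded by the rule (38, 36 or 34 left) it is 0.990, 0.987 or 0.982. The question is bias.

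**Opportunity to qualify.**
- Intervention arm: 8 + 3 = 11 to 24 + 3 = 27 sessions. Control arm: 3.
- Control patients have from baseline (6–12 weeks before surgery) to about week 4 without a session, that is 6 − 4 = 2 to 12 − 4 = 8 weeks. Anyone leaving in that window is excluded.
- An intervention patient who leaves in the same window after one training session stays in.
- How often this happens depends on when training starts, which the article does not state. Eight sessions between week 4 and the 1-week pre-operative visit would need 8 / 3 = 2.7 a week, so a short programme could start as late as the knee school. Twenty-four would need 24 / 3 = 8 a week, so long programmes must start earlier.

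**Size under assumptions.** Let *q* be the share of an arm excluded, and *D* the gap, in SD units, by which excluded patients would have improved less than retained ones. The full-arm mean is (1 − *q*) × retained mean + *q* × excluded mean, so the retained mean exceeds the full-arm mean by *q* × *D* × SD. With the same *D* in both arms:

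bias in the difference = (*q* intervention − *q* control) × *D* × 7.3 s

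For type I error, the shift in SD units is divided by √(1/n₁ + 1/n₂), where n₁ and n₂ are the patients left of 40 per arm, and compared with ±1.96. The values of *q* and *D* are assumptions; the article gives none.

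| Excluded, one arm vs the other | *D* | Absolute shift | Share of 7.3 s | Two-sided type I error |
|---|---|---|---|---|
| 0% vs 5% | 0.5 | 0.05 × 0.5 × 7.3 = 0.18 s | 2.5% | 0.051 |
| 0% vs 5% | 1 | 0.05 × 1 × 7.3 = 0.365 s | 5.0% | 0.056 |
| 2.5% vs 10% | 0.5 | 0.075 × 0.5 × 7.3 = 0.27 s | 3.8% | 0.053 |
| 2.5% vs 10% | 1 | 0.075 × 1 × 7.3 = 0.55 s | 7.5% | 0.062 |
| 0% vs 12.5% (5 of 40) | 0.5 | 0.125 × 0.5 × 7.3 = 0.46 s | 6.3% | 0.058 |
| 0% vs 12.5% (5 of 40) | 1 | 0.125 × 1 × 7.3 = 0.91 s | 12.5% | 0.084 |

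The sign follows the arm that loses more patients and the sign of *D*. If the poorer prospects leave mainly from the control arm, the estimate shrinks; if mainly from the training arm, it grows. If *q* and *D* are equal in the two arms, the shift is zero and type I error stays at 0.05.

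**The case against.** The rule is announced in advance, sets the same minimum in words for both arms, and stands apart from the per-protocol analysis. Everyone randomised has already consented and completed baseline, so non-attenders may be few. Knee school is offered to both arms at about the same time, and one session is enough. The planned adjustment for baseline function, age, gender and body mass index would remove part of any prognostic difference. All of this stands, and it limits the likely size. It does not make the set intent-to-treat or remove the conflict with the Design section. One could also read the word that introduces the condition as illustrative rather than restrictive, but then the sentence would say nothing about who is in the set and would still need rewording.

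Four stronger readings are tempting, and the document does not support them:
- *That the randomised comparison is lost or the estimate is biased.* No non-attendance rate is given, and nothing shows that exclusion will in fact depend on arm and prognosis. The bias is possible, not shown.
- *That training must always start before week 4.* This is clear only for long programmes; no start date or weekly frequency is stated.
- *That the planned 12% drop-out measures the loss.* That figure is for the trial generally. Placing all of it before the first session and in one arm is an upper case.
- *That trained patients will postpone surgery and drop out of the 3-month comparison.* The Background remark that exercise may delay joint replacement is general. These patients have decided on surgery and are on the waiting list, and the article gives no number who might postpone. Any such shift could run against the one above, so the two cannot simply be added.

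**Conclusion.** The sentence is wrong as written. It defines a modified intent-to-treat set, calls it intent-to-treat, and contradicts the unconditional statements in the Design and Discussion sections. Because the article itself fixes the set for all analyses, this is not a detail left to a separate analysis plan.

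That exclusion can differ between the arms follows from three features of the design: known allocation, an undefined qualifying session, and arms that differ in the type, number and possible start of sessions. The resulting bias is a possibility of unknown size and direction. Under the moderate assumptions it is about 0.2–0.55 s, with type I error of 0.051–0.062. The upper case is about 0.9 s (12.5% of the assumed effect), with type I error of 0.084. These figures rest on assumed exclusion rates and an assumed gap of 0.5–1 SD, and they ignore the covariate adjustment. All are small against 7.3 s, and they would weigh more if the true effect were smaller than assumed.

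**What to change.** 1. Delete the attendance condition that closes the first sentence of the Analysis plan, and define the primary set as all randomised patients, analysed in the arm to which they were allocated.
2. Invite patients who attend no session to the outcome visits already scheduled. Without this the new wording changes little, since a patient with no outcome measured adds nothing to the regression.
3. Keep the at-least-one-session set as a sensitivity analysis, named modified intent-to-treat, and state for each arm which sessions count.

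The planned regression and the visit schedule can stay as they are. Adherence already has its own place in the per-protocol analysis and in the subgroups by number of sessions attended. The cost is a change of wording, some extra effort to follow the non-attenders, and possibly a slightly smaller estimate because untreated patients are counted. The change should be made before anyone is excluded under the present rule.
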